# The OPTIMISE project: protocol for a mixed methods, pragmatic, quasi-experimental trial to improve primary care delivery to refugees in Australia

**DOI:** 10.1186/s12913-019-4235-6

**Published:** 2019-06-19

**Keywords:** Migrant health, Refugee health, Primary health care, Primary care, Partnerships, Intervention trial

## Abstract

**Background:**

Australia is one of many nations struggling with the challenges of delivering quality primary health care (PHC) to increasing numbers of refugees. The OPTIMISE project represents a collaboration between 12 organisations to generate a model of integrated refugee PHC suitable for uptake throughout Australia. This paper describes the methodology of one component; an outreach practice facilitation intervention, directed towards improving the quality of PHC received by refugees in Australian general practices.

**Methods:**

Our mixed methods study will use a cluster stepped wedge randomised controlled trial design set in 3 urban regions of high refugee resettlement in Australia.

The intervention was build upon regional partnerships of policy advisors, clinicians, academics and health service managers. Following a regional needs assessment, the partnerships reached consensus on four core areas for intervention in general practice (GP): recording of refugee status; using interpreters; conducting comprehensive health assessments; and referring to refugee specialised services.

Refugee health staff trained in outreach practice facilitation techniques will work with GP clinics to modify practice routines relating to the four core areas.

36 general practice clinics with no prior involvement in a refugee health focused practice facilitation will be randomly allocated into early and late intervention groups.

The primary outcome will be changes in number of claims for Medical Benefit Service reimbursed comprehensive health assessments among patients identified as being from a refugee background. Changes in practice performance for this and 3 secondary outcomes will be evaluated using multilevel mixed effects models.

Baseline data collection will comprise (i) pre-intervention provider survey; (ii) two surveys documenting each practices’ structure and approaches to delivery of care to refugees. De-identified medical record data will be collected at baseline, at the end of the intervention and 6 and 12 months following completion.

**Discussion:**

OPTIMISE will test whether a regionally oriented practice facilitation initiative can improve the quality of PHC delivered to refugees. Findings have the potential to influence policy and practice in broader primary care settings.

**Trial registration:**

Australian New Zealand Clinical Trials Registry, ACTRN12618001970235, 05/12/2018, Retrospectively registered.

Protocol Version 1, 21/08/2017.

**Electronic supplementary material:**

The online version of this article (10.1186/s12913-019-4235-6) contains supplementary material, which is available to authorized users.

## Background

Australia is a major site for the resettlement of refugees. Over 78,000 permanent resident visas were granted to refugees and asylum seekers between 2011 and 2016 [1, 2]. The nation’s refugee and humanitarian program intake has recently increased (in 2018/19) to 18,750 per annum [2], the majority of whom will settle in the states of New South Wales and Victoria [3, 4].

The vulnerability of Australians of a refugee background follows from the physical and psychological sequelae of torture, trauma and multiple deprivations in countries of origin and transit [5]. Compared to the wider population, refugees are at greater risk of mental health conditions [6], infectious disease [7], nutritional deficiencies [8], obstetric complications [8], poor dental health [9] and disability [10]. Complex physical and psychological problems are often addressed only for the first time in Australia [11].

Australian states and territories have introduced different approaches to aid transition to life in a new country [3, 4]. Pathways vary across regions within different states/territories, and, as to whether refugees arrive through a sponsored or non-sponsored pathway. However, in general, resettled refugees are initially put in contact with Commonwealth funded Humanitarian Settlement Program service providers, which provide practical assistance for settling in the community. In many jurisdictions, new arrivals may be directed to Refugee Focused Health Services and/or a mainstream General Practice for initial health assessment [12]. Subsequently, all but the most complex clients are managed within mainstream primary care.

The health and wellbeing of people of refugee background is intimately linked with their ability to access high quality, coordinated primary health care [12]. Many struggle to access general practitioners, specialists, community health services and hospitals – problems related to socio-economic factors, language and cultural differences and the complexity of the Australian healthcare system [3, 4]. Provision of quality care to refugee background patients in mainstream primary care has been found to be inconsistent, with many providers having incomplete knowledge of refugee health requirements. Interpreters are underutilised, [5], coordination between sectors problematic, and, at times, in some jurisdictions, Refugee Focused Health Services have found it difficult to provide timely care [13, 14].

Outreach practice facilitation has become a promising intervention to support quality improvement in primary care [15]. Practice facilitation has been shown to improve chronic disease management, increase prevention, and facilitate system-level change and quality improvement [16]. Emerging evidence has shown that the principles of outreach practice facilitation could assist in the care of vulnerable populations, including refugees [17, 18]. This protocol outlines a project designed to investigate the effectiveness of outreach practice facilitation in supporting primary care practice-wide quality improvement within the context of refugee health.

### Objectives

Our overall objective is to conduct a mixed methods evaluation of a practice facilitation intervention designed to improve the primary care management of refugees in 36 general practice clinics across 3 regions: South East Melbourne (SEM), North West Melbourne (NWM) and South West Sydney (SWS).

We asked whether a facilitation-based intervention directed at improving the quality of general practice-based primary care delivered to patients with a refugee background could increase:The conduct and documentation of comprehensive physical and mental health assessments among patients identified as being from a refugee background (primary outcome)

Secondary outcomes:2.Refugee status determination and recording3.The use of credentialed interpreters among patients identified as being from a refugee-like background4.Practice staff knowledge and use of referral pathways to refugee specific health and social welfare services

## Methods

### Study design

This quality improvement programme has a mixed methods approach incorporating a cluster randomised controlled trial (cRCT) design with blind allocation to early and late intervention groups [19]. Quantitative measures collected cross-sectionally at multiple timepoints will be assessed using the recommended statistical approach for step-wedged cRCT designs [20]. An embedded qualitative component will explore the acceptability, usefulness and sustainability of the intervention(s).

The study will be informed by the literature on organisational change that identifies the factors influencing the diffusion and institutionalisation of organisational innovations, and where organisations are considered as a whole rather than as a set of independent attributes [21–23]. Two principles underpin the study design: a) Participatory research: where community based research partnerships built upon on-going knowledge exchange are considered an essential component of sustainable innovations and, community impact [24, 25]; and b) Implementation science: incorporating contemporary approaches to quality improvement, and, in particular Normalization Process Theory’s principles for understanding the process of embedding change in a practice by examining what people actually do and how they work [26].

### Study setting

The study will be conducted in general practice clinics in two regions of metropolitan Melbourne and one region in metropolitan Sydney, each with high rates of refugee resettlement. The study regions correspond to the Commonwealth Government Primary Health Networks (PHN) regions of South East Melbourne, North West Melbourne and South West Sydney [27].

### Sample

Trial eligibility is at three levels. Participating general practice clinics will be located in one of the three PHN regions, provide general primary care services and plan to be in operation for the next two years without substantial change to governance or management. Each will have needed to be in operation for 12 months and use electronic medical records and billing software compatible with the study’s data extraction tool (PENCS CAT4**™**). Practices will not have participated in refugee health related capacity building activities in the 12 months immediately preceding the study.

At least 50% of GPs in a practice must consent for practice participation to be confirmed. As the intervention is designed around a whole-of-practice approach, the research team will ensure there is a process by which staff within the practice can confidentially object to the practice’s participation in the study, via call or email. If this occurs, the practice will be withdrawn from the study.

### Intervention

#### Development of the intervention

The oversight of the study’s activities in each region is the responsibility of regional partnership teams (RPTs) comprising decision makers, clinicians, academics, health service managers and community members (Table 1).

**Table 1 Tab1:** Participating organisations

Regional Partnership	Academic Institutions	Primary Health Organisations	Refugee Focused Health Services	Settlement agencies	State based organisations	National organisations
South East Melbourne	Monash University	Enliven Victoria 2016–2017: South Eastern Health Providers Association	Monash Health Refugee Health and Wellbeing	AMES Australia	Victorian Department of Health and Human Services Victorian Refugee Health Network	Royal Australian College of General Practitioners Refugee Health Network of Australia
North West Melbourne	La Trobe University	North Western Melbourne PHN.	cohealth			
South West Sydney	University of New South Wales	South Western Sydney PHN.	NSW Refugee Health Service	Settlement Services International	NSW Refugee Health Service	

Each RPT worked to characterise each region’s policy, program and service context with particular reference to the care of refugee populations. We focused specifically on barriers and enablers affecting access, transition and quality of primary care within the region. To further understand regional partnership needs, each RPT performed a focused scientific and grey literature review, analysed secondary data extracted from the Australian Bureau of Statistics Census, Department of Home Affairs Settlement Reporting Facility, settlement agencies, public health services and local councils, and conducted a series of key informant interviews with health service managers, policy advisors and clinicians. The three RPTs then met in a deliberative forum [28] to determine priority interventions, from which four core areas of activity were chosen;Physical and mental health assessments: GPs and practice nurses will have relevant skills and knowledge to conduct comprehensive refugee physical and mental health assessments.Refugee identification: general practice clinics will have accurate and accessible mechanisms in place to record and retrieve refugee identification, status, country of birth or ethnicity, year of arrival, and need for interpreter.Use of interpreters: practices will have a practice protocol for using interpreters, and ensure that staff have appropriate knowledge and skills in their role of supporting use of interpreters**.**Referral pathways: practice staff will gain an understanding of refugee health referral pathways in the region (including available services, eligibility requirements and referral procedures).

These areas of focus helped the study objectives (see above). All practices recruited will be asked to work on these four core areas as a minimum, with the option to choose an additional 1–2 activities from a list of optional tasks depending on interest and capacity (Table 2).

**Table 2 Tab2:** Intervention Optional activities

Activity	Description
Cultural awareness	Practice staff demonstrate cultural awareness and sensitivity to refugee issues, including an understanding of the refugee experience.
Communication skills	GPs and practice nurses have appropriate communication skills (They are sensitive to the needs of refugees and take time to explain care to patients so they can make informed decisions by understanding what is happening as part of their care).
Business practices	practice staff are knowledgeable about and use business practices (including longer appointments, booking appointment with specific GP, Medicare billing, etc.) to support conduct of refugee health assessments
Information sharing	Practice has in place clear processes for sharing relevant patient information with other services. Practice staff use these processes consistently when receiving patient information and obtaining patient information.
Follow up on referrals	Practice staff refer clients to appropriate services and check whether the client attended the service. (If the problem is urgent or clinically significant this follow up may be with the receiving service, otherwise, follow-up will occur when patient re-attends the clinic)
Clinical matters	Practices may also identify other areas related to the clinical care of refugees. GPs and practice nurses may choose to learn more about the diagnosis and management of specific refugee health issues, e.g. refugee catch-up immunisation, mental health, paediatric health, infectious diseases.

#### Intervention process

Practice Facilitators will deliver the intervention to general practice clinics using a plan/do/study/act (PDSA) approach oriented to the four core goals [29]. Practice Facilitators will make a minimum of three, 60–90 min, in-person contacts with each participating practice during the six-month intervention period. Practices will receive one telephone contact following each visit.

Prior to the intervention commencing, each practice will identify a team comprising the practice lead and key practice participants, including at least one GP and (if applicable) one practice nurse. The team will complete a survey designed to ascertain current practice performance and needs in key areas of refugee health. This information will be used to help the Practice Facilitator lead a discussion during their first visit to the practice where the practice team will identify and discuss potential needs and areas for action, and develop an action plan (following a pre-designed template) for each of the four core priority areas. The action plans were adapted from the Victorian Refugee Health Network’s *Engaging and supporting General Practice in refugee health* program [18] and an example can be found in Additional file 1.

The subsequent two practice facilitation visits and phone calls will act to support and monitor action plan development and implementation. The Practice Facilitator will continue to assist with challenges faced by the practice and identify any other resources, strategies, tools or training available to aid in the action plan’s implementation.

Practices will also be provided with additional resources relating to the four core priority areas, including a soft and hard copy of a “General Practice Resource Book”. This book was created by the research team to provide a directory of verified resources organised to complement the four goals targeted by the project. A two-page electronic ‘summary sheet’ of key resources, with links embedded to be easily accessed on electronic devices, will also be provided.

#### Intervention providers

Practice Facilitators will be existing refugee health staff in each region and will be refugee health clinical fellows,^1^ refugee health nurses^2^ or project officers currently employed by Refugee Focused Health Services. Each will need to have experience in refugee and asylum seeker health care delivery and an understanding of the principles of engaging general practice clinics in quality improvement activities. This knowledge as well as the tasks and timelines of the role will be reinforced by a one-day training program and on-going facilitator support meetings. The content of the training was based on findings from the North-West Melbourne Primary Health Network’s in-house GP support program, the Settlement Coordinators’ program, and the Victorian Refugee Health Network’s *Engaging and supporting General Practice in refugee health* program. Additional material was sourced from the Agency for Healthcare Research and Quality training program for outreach practice facilitation [30] and the researchers’ prior work in other facilitation initiatives [31–33].

### Outcomes

The primary outcomes will be changes in number of claims for the delivery of Medicare Benefits Schedule (MBS) reimbursed comprehensive health assessments among patients identified as being from a refugee background. We will calculate the change in proportion of eligible (within 12 months of arrival in Australia) refugee background patients with medical records where there is evidence of billing for a comprehensive health assessment (MBS items 701, 703, 705 and 707). Secondary outcome measures will be:(i)The change in the proportion of patients with records with recorded refugee identification (country of birth, ethnicity, year of arrival).(ii)The change in proportion of refugee patient consultations with documented use of credentialed interpreter, where one was required.(iii)The change in practice staff knowledge, attitudes and behaviours towards referring refugee background patients to external health and welfare services for which their refugee patients are eligible.

We will also measure changes in general practitioners’ confidence to undertake health assessments, catch-up immunisation and infectious diseases screening, and changes in practice routines relating to health assessments.

### Participant timeline

A timeline of the intervention proposal is shown in Table 3.

**Table 3 Tab3:** Intervention Timeline

Month	Pre-intervention		1st month Facilitation	2nd Facilitation	3rd Facilitation	4th Facilitation	5th Facilitation	6th Facilitation	7th mth	8th	9th	10th	11th	12th m	13th	
	July – August & ongoing as required	August ongoing	Grp 1 September +	Oct +	November +	December +	January +	Feb +	March +	April	May	Jun	July	August	Sept 2018 +	
			Grp 2 March 2018 +	Apr +	May +	Jun +	July +	Aug +	Sept +	Oct	Nov	Dec	Jan	Feb	March 2019 +	
Activity	Recruitment of 12 practices	Baseline data collection (with all practices following consent)	Practice facilitation visit #1 (Doesn’t commence until consent confirmed, & practice survey completed)	Follow up and phone call #1	Practice facilitation visit #2	Follow up phone call #2	Practice facilitation visit #3	Follow up phone call #3	Post intervention data collection			Practices conduct business as usual				6-month post intervention data collection
Description	Includes all contact up to the point of gaining informed consent from the practice and staff (GPs, nurses and others). Open and targeted invitations. Informed by RHN, RHFs, others. EOI form completed & eligibility checked.	Randomise practices to immediate start or wait. Visit ALL practices as they are recruited to finalise consent and confirm data collection processes, including PEN CAT and TIS. Make appointments for PENCAT data collection Sign consent form for TIS data Commencing Practices Explain to practice manager that on line surveys must be completed before facilitation can commence: -Practice survey -Clinicians: at least 50% of GPs. WAITING practices (6 month wait): RO Also Completes Refugee healthcare survey with practice team. Facilitator not present.	Step 1. Pre intervention refugee healthcare (RHC) survey conducted by RO with practice team to identify potential areas for action Facilitator observes and takes notes to assist them with step 2. Step 2. Facilitator leads discussion with practice team informed by the RHC interview and practice description survey. Purpose is to a) identify and discuss action areas aligned to intervention priorities, b) to commence action plan development WAITING practices (6 month wait): Refugee healthcare survey is REPEATED with practice team and step 2 undertaken when they commence facilitation.	Prior to phone call send practice draft action plans (based upon learnings from refugee health survey) The practice reviews action plans, edit if required and return to facilitator. Practice implements action plans. Phone Call- Review progress with action plan development and early challenges with action plan implementation.	Provide support for action plan development and implementation and monitor implementation	Provide support for action plan implementation and monitor implementation Document changes to the action plan that have occurred.	Provide support for action plan implementation and monitor implementation Document changes to the action plan that have occurred.	Provide support for action plan implementation and monitor implementation Document changes to the action plan that have occurred.	PENCAT data extraction Post intervention RHC survey			New practices & procedures operate				PENCAT data extraction Post intervention RHC survey/ interview

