### Assignment of interventions

#### Allocation

Following recruitment into the study, practices will undergo blinded, stratified random allocation into either an early or late intervention group using a minimization procedure. Early group practices will start receiving the intervention immediately after recruitment. Late group practices will start the intervention 6-months after the date of completing the initial baseline data collection to act as control for the group receiving the intervention first. To ensure that early and late study groups are similar, practices will be stratified based on region and practice size as determined by the number of full time equivalent (FTE) general practitioners (≤ 5 FTEs, > 5 FTEs). The randomization codes were generated using Minim randomization software [35]. Wherever possible, batches of two or more practices will randomised at the same time.

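### The first Refugee healthcare survey is taken with the facilitator observing in early practices and without the facilitator in late practices, yet both count as baseline

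*Protocol article*

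**What the plan says.** **The survey.** In Participant timeline, Table 3, the pre-intervention column tells the research officer what to do in waiting practices: "RO Also Completes Refugee healthcare survey with practice team. Facilitator not present". Early practices have no such step there. Their only pre-intervention Refugee healthcare survey is step 1 of the first facilitation visit. The research officer runs it with the practice team, and "Facilitator observes and takes notes to assist them with step 2". Step 2 is the discussion that the facilitator leads. Waiting practices repeat the survey when their own facilitation starts.

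Data collection methods defines baseline as a point before the intervention starts. The list of instruments in the same section places this survey within the first facilitation visit. Statistical methods codes timepoint 0 as baseline for all practices. It codes timepoint 1 as post-intervention for early practices and pre-intervention for late practices.

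**The order of steps.** The column of Table 3 that holds randomisation opens with "Randomise practices to immediate start or wait. Visit ALL practices as they are recruited to finalise consent and confirm data collection processes". It then lists the extract appointments and the surveys. The column before it "Includes all contact up to the point of gaining informed consent from the practice and staff (GPs, nurses and others"), and the randomisation column is itself headed "Baseline data collection (with all practices following consent"). Facilitation "Doesn’t commence until consent confirmed, & practice survey completed". Allocation states: "Following recruitment into the study, practices will undergo blinded, stratified random allocation". Sample states: "At least 50% of GPs in a practice must consent for practice participation to be confirmed", and it withdraws a practice if a member of staff objects.

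**The concern.** A baseline is useful only if both arms are measured in the same way. This survey is a practice team's account of its own approach to refugee care. According to Intervention providers, the facilitators come from Refugee Focused Health Services in the region. An early practice therefore describes its routines in front of such a person, at the start of a visit meant to improve those routines, and knowing its allocation. A late practice describes its routines to a research officer alone. Answers could move either way: a team may present itself better in front of the facilitator, or admit gaps more readily because help is on offer. Any such shift at baseline carries into the early-late comparison of change.

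At stake are the measures drawn from this survey: practice routines, and referral only if this instrument measures it (Additional file 4 is not shown).

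The wording on order matters for a second reason. If consent or baseline is completed after a practice knows its allocation, that knowledge can influence both.

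**Working it through.** The plan gives no figure on this point to reproduce. The check sets the sections side by side and then traces how a shift at timepoint 0 enters the main model.

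**1. Conditions of each pre-intervention survey (Table 3; codes from Statistical methods)**

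| | Early, only survey | Late, first survey | Late, repeat |
|---|---|---|---|
| Setting | Facilitation visit 1, step 1 | Baseline phase, before facilitation | Start of facilitation |
| Run by | Research officer | Research officer | Not stated |
| Facilitator | Present, taking notes | Absent | Not stated |
| Timepoint code | 0 | 0 | 1 |

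The two surveys that share code 0 differ in setting and in facilitator presence. The late survey whose setting looks most like the early one carries code 1.

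**2. Is the early survey a baseline by the plan's own definition?** Visit 1 is one of the minimum of three in-person contacts that make up the intervention (Intervention process). A survey inside it is not clearly before the intervention, as Data collection methods requires. Intervention process also has the team complete a survey of performance and needs before the intervention begins. It does not name that survey, so this last conflict is likely rather than certain.

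**3. Weight of timepoint 0.** Assume that the main model (fixed effects for group, categorical timepoint and intervention status) is used for these measures. The Abstract extends mixed models to the secondary outcomes, but practice routines are not named. Let d0, d1 and d2 be the early-minus-late differences at timepoints 0, 1 and 2, g the group effect and θ the intervention effect.

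- Timepoint 0, neither arm exposed: d0 = g
- Timepoint 1, early exposed only: d1 = g + θ
- Timepoint 2, both exposed: d2 = g
- Timepoint 3, late practices only: absorbed by its own time effect

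With equal variances and equal correlations, θ is estimated by d1 − (d0 + d2)/2, so d0 has weight −0.5. This needs an early-practice survey 6 months after the intervention. Table 3 lists one (as survey/interview); Table 4 does not. Under Table 4, d2 does not exist, θ is estimated by d1 − d0, and d0 has weight −1.

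**4. Effect of a shift b (assumed; no value is given).** If facilitator presence moves answers by b, d0 moves by b, which contributes −0.5b under Table 3 or −b under Table 4. If the facilitator also attends the late repeat, d1 moves by a further −b. With all post-intervention surveys taken without the facilitator, the totals become −0.5b − b = −1.5b or −b − b = −2b. If the facilitator is also present at the early post-intervention survey, d1 moves by +b and offsets part of this. The plan does not state the conditions of these later surveys.

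**5. What is not exposed.** The primary outcome is billing evidence in extracted records. Identification and interpreter use also come from extracts. Table 3 has commencing practices complete the practice and clinician surveys online before facilitation.

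**6. Order of allocation and consent.** Consent first: the recruitment column of Table 3, the heading of the randomisation column, Recruitment and Allocation. Randomisation first: the order of sentences inside one cell of Table 3. That cell also gives commencing and waiting practices different baseline tasks, so those tasks can be assigned only once allocation is known to the team. No section says that baseline data precede allocation.

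**The case against.** The strongest reply is that the research officer administers the survey in both arms and that, in early practices, it comes before the facilitator says anything of substance. Late practices also repeat it at the start of facilitation, apparently in a similar setting. This reduces the concern but does not remove it. The difference lies in who is listening, not only in what has been taught. The repeat belongs to timepoint 1, where it serves as control data, so it does not correct the mismatch at timepoint 0.

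A second reply is that the model's group term absorbs a baseline difference. It does, but as a lasting difference between arms. A difference caused by the conditions of one survey is then wrongly subtracted from the later comparison, as the weights above show.

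On the order of steps, a reader might infer that the plan fixes randomisation before consent. The documents do not support that. Most of the relevant text puts consent first, the visit is made as practices are recruited, and finalising consent may mean remaining items such as the interpreter-data form in the same cell. What stands is that the text is inconsistent.

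A reader might also infer that practices will leave after learning their allocation and so undo the randomisation. No loss rate, overall or by arm, is given. With an equal split, one practice is 1/18 = 5.6% of an arm (36/2 = 18), but that describes arm size and is not an estimate of bias. The staff-objection rule is a safeguard that can operate at any time, whatever the order of steps.

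**Conclusion.** The point holds for one instrument. Followed as written, Table 3 measures the first Refugee healthcare survey differently in the two arms, after allocation is known to the team, and Statistical methods treats the results as a common baseline. Comparisons of change in that survey's measures can be biased in either direction. The size cannot be derived: only the weight on the timepoint 0 shift can be given, −0.5 to −1, assuming that the main model is applied and depending on whether Table 3 or Table 4 is right about the 6-month survey.

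It would be wrong to read this as making all survey baselines non-comparable or as touching the primary outcome. Facilitator presence is documented for this survey only, and for early practices only at the first administration; for the late repeat it is not stated. The order of consent, baseline and allocation is a drafting inconsistency to be reconciled. Loss of practices after allocation is a possible risk that the documents neither show nor size.

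**What to change.** Have the research officer run the first Refugee healthcare survey without the facilitator in both arms, at the visit already planned for all practices and before allocation is made or disclosed. Pass the completed form to the facilitator for the step 2 discussion. Run the late-group repeat under the same conditions, and state the conditions of the post-intervention surveys.

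In Table 3, state that practice consent, consent of at least 50% of GPs and baseline collection come before randomisation. Leave the staff-objection safeguard open at any time. Align Intervention process, both parts of Table 3, Allocation, Data collection methods and its list of instruments, and reconcile Tables 3 and 4 on the 6-month survey.

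The calendar in Table 3 runs to March 2019, before the article appeared in June 2019, so for many practices the steps may already be past. For practices already enrolled, record and report facilitator presence at each survey and the actual order of consent, baseline and allocation.

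The cost is small: the facilitator works from a form instead of observing, and the start in early practices may be slightly delayed.
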